#### Planning, engaging, executing, evaluating, and reflecting cycles

We will make frequent changes to the peripheral components of the intervention through co-occurring cycles of planning, engaging, executing, evaluating, and reflecting (PEEER) initiated by nurses, the internal facilitator, or other research and clinical staff [16]. PEEER is the process through which adaptations to peripheral components of the intervention occur. This implementation strategy is often referred to as cyclical small tests of change [25]. PEEER may continue informally after implementation, leading to ongoing adaptations if needed.

#### Internal facilitation

The research coordinator, who has worked with the MUHC nurses on other projects, will serve as an internal facilitator and oversee the PEEER cycles. The internal facilitator will be available to nurses as needed, to address urgent barriers to implementation and to make time-sensitive adaptations when necessary. The study investigators will be consulted regularly and support the internal facilitator in engaging clinic stakeholders and ensuring timely adaptations. Regular and ongoing tasks carried out by the study team (investigators and internal facilitator) will be transferred to clinic staff at the end of the implementation phase/start of the sustainability phase.

## Research study aims

This quasi-experimental pilot study will follow a type II implementation-effectiveness hybrid design [27]. In type II implementation-effectiveness hybrid studies, the intervention and implementation strategy are given equal consideration and simultaneously evaluated. Alternatively, in type I and type III designs, the intervention and the implementation strategy, respectively, represent the primary focus for evaluation [27]. Fitting our need to both contribute to the evidence base on effectiveness for our intervention and test a combined implementation strategy, we chose a type II design. As a pilot study, we will learn whether the implementation of the intervention shows promise, possibly leading to a more rigorous evaluation using a randomised trial.

We envision implementing Lost & Found over twelve months followed by a sustainability phase of three months. This three-month period will provide time to document ongoing effectiveness and identify further changes that could help ensure long-term sustainability. All activities prior to implementation are considered part of the pre-implementation phase [21].

Under the overall objective of determining the viability of a multisite stepped-wedge cluster randomised trial, this study has two primary aims:
Aim 1: To assess interim effectiveness and implementation outcomes of the Lost & Found intervention.Aim 2: To evaluate the cumulative effectiveness and short-term sustainability of the Lost & Found intervention.

## Methods

### Setting

The McGill University Health Centre (MUHC) is a large public quaternary care hospital in Montreal, Canada. Multidisciplinary care for adult patients with chronic viral illnesses such as HIV and chronic hepatitis C virus is provided at the Chronic Viral Illness Service (CVIS) clinic. Over 90% of patients who received care at the CVIS in 2018 were PLHIV (*n* = 1777). A variety of services are offered within the clinic including care by infectious disease and other specialists, family physicians, nurses, pharmacists, social workers, a psychologist, and a psychiatrist. The MUHC has a hospital-wide electronic medical record for all patients (OACIS) as well as one specifically designed for the CVIS (RISQ).

### Aim 1: To assess interim effectiveness and implementation outcomes

#### Overview

A convergent parallel mixed-methods approach will be used. Qualitative data on nursing-related implementation outcomes will be collected using focus groups, and a logbook maintained by the research coordinator/internal facilitator will document implementation and intervention changes throughout implementation. Quantitative data will also be collected using questionnaires to assess implementation outcomes and through RISQ, which will provide data on interim effectiveness outcomes. A mixed-methods analysis will allow for a more complete understanding of the impact of changes made to peripheral components of the intervention over time [28]. Implementation outcomes will help inform utility of the implementation strategy and serve as intermediate outcomes for interim effectiveness of the intervention, consistent with Proctor’s framework [23].

#### Participants

Participants will include all nurses providing clinical HIV care to patients over the study period (*n* = 4). For interim effectiveness outcomes, all PLHIV registered in the RISQ database during the 12-month implementation phase will be included. Patients who have not had an HIV care visit at the clinic within five years of the start of the study will be excluded.

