#### Outcomes and related measures

##### Effectiveness

Information to evaluate changes in interim effectiveness outcomes over time will be collected automatically using RISQ and will be extracted for analysis at specific time points during the study (see Table 2). Interim effectiveness refers to effectiveness between the time points in Table 2, as opposed to cumulative effectiveness, which refers to overall effectiveness for the implementation or sustainability phases. These interim effectiveness outcomes include the number of patients identified and confirmed as OOC by nurses. Among OOC patients, we will report the number of patients contacted, successfully re-engaged, and not re-engaged, as well as reasons for lack of care re-engagement. For each OOC-RPT risk category, and overall, we will also provide the number of contact attempts needed to re-engage patients, time to re-engagement, and other clinical and sociodemographic information routinely collected in RISQ.

**Table 2 Tab2:** Data collection schedule

	Pre-implementation	Week 1	Week 2	Week 3	Week 4	Month 2	Month 3	Month 6	Month 12	Month 15
Effectiveness					d	d	d	d	d	d
Feasibility	a, c				a, c	a, c	a, c	a, c	a, c	c
Acceptability	a, c				a, c	a, c	a, c	a, c	a, c	c
Adoption	a, c				a, c	a, c	a, c	a, c	a, c	c
Fidelity	b, c	b	b	b	b, c	b, c	b, c	b, c	b, c	c

a) 36-item questionnaire; b) fidelity checklist; c) focus group; and d) RISQ

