#### Participants

All MUHC patients in the RISQ database during the 12-month implementation phase and the first three months of the sustainability phase will be included in analysis i). For analysis ii), we will retrospectively apply the OOC-RPT, excluding the nurse validation step, to patients in the year prior to implementation in order to create a pre-implementation comparison group. Thus, we will include all patients categorised as OOC by the OOC-RPT from one year prior (2017-2018) and to the end of the implementation phase (late 2019) in this analysis. Patients labelled as OOC before or after this time frame will receive the Lost & Found intervention, but will be excluded from the analysis because they did not become OOC within the time frame of the analysis. Based on the number of patients who were identified as not having had care appointments in 2016, we estimate approximately 25–30 patients will be identified as potentially OOC each month during the implementation of Lost & Found. In analysis iii), MUHC patients categorised as OOC from three months before the end of the implementation phase to the end of the sustainability phase (three months) will be included.

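### Aim 1 interim effectiveness and descriptive analysis i mix patients already out of care at go-live with those who become so later, so trends over time can reflect a one-off backlog

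*Protocol article*

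**What the plan says.** All references are to the protocol article.

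- **Aim 1 population** (Aim 1, Participants): "all PLHIV registered in the RISQ database during the 12-month implementation phase will be included". The one exclusion is "Patients who have not had an HIV care visit at the clinic within five years of the start of the study will be excluded". Patients absent for less than five years therefore stay in, whenever they became OOC.
- **Analysis i population** (Aim 2, Participants): "All MUHC patients in the RISQ database during the 12-month implementation phase and the first three months of the sustainability phase will be included". The five-year limit is not restated. Aim 2, Effectiveness, says that analysis i reuses the Aim 1 measures, once for months 1 to 12 and once for months 12 to 15.
- **Purpose** (Aim 1, Effectiveness): "Information to evaluate changes in interim effectiveness outcomes over time will be collected automatically using RISQ", and "Interim effectiveness refers to effectiveness between the time points in Table 2". Those time points are week 4 and months 2, 3, 6, 12 and 15.
- **Outcomes** (same section): the number identified and confirmed as OOC, then "Among OOC patients, we will report the number of patients contacted, successfully re-engaged, and not re-engaged". Contact attempts and time to re-engagement are reported by risk category and overall. No other split is stated.
- **Analysis ii** (Aim 2, Participants), by contrast, limits patients by when they became OOC: "Patients labelled as OOC before or after this time frame will receive the Lost & Found intervention, but will be excluded from the analysis", the reason given being "because they did not become OOC within the time frame of the analysis".

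**The concern.** When the tool first runs it flags everyone who already meets the OOC rule, including people who have been away for a long time. That group enters once. Patients who become OOC later arrive as a steady flow. A series of extractions that pools the two starts with a mixture heavy in backlog and moves towards newly OOC patients, whatever the nurses do.

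The Aim 1 Overview says that the mixed-methods analysis is meant to show the impact of changes to peripheral components over time. The change in case mix falls in the same early months as the most frequent questionnaires and focus groups, when adaptation is expected to matter most. A shift caused by the make-up of the list could not be told apart from a shift caused by adaptation. The months 1 to 12 and months 12 to 15 summaries of analysis i would likewise describe different mixtures.

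**Working it through.** **Step 1: is there a backlog, and is it counted?**

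- Background: since 2015, 10% of registered patients a year have not returned, and there was no formal system to re-engage them.
- Core element I: step 1 of the tool classifies all patients with HIV every day, so those already overdue are flagged as soon as it runs.
- Aim 2, Participants: patients labelled OOC before the analysis ii time frame still receive the intervention.
- Neither Aim 1 nor analysis i sets a condition on OOC onset, so these patients are counted there. Risk category rests on clinical characteristics and does not separate old absences from new ones.

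**Step 2: inputs for an illustration.** The plan gives no backlog size and no re-engagement rates, so there is no figure of its own to reproduce.

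- From the document: 1777 patients with HIV in 2018 (Setting); 10% a year; 25 to 30 patients identified a month (Aim 2, Participants), midpoint 27.5, used here as the flow of new cases.
- Leavers: 0.10 × 1777 = 178 a year, or 4 × 177.7 = 711 over four years if none returned.
- Assumed: backlog B between 90 and 710; re-engagement 50% for new patients and 20%, 35% or 50% for backlog patients, constant over time; backlog confirmed 40/20/15/15/10/0% over the six intervals, each patient counted once.

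**Step 3: formula.** In an interval with b backlog and n new patients, crude re-engagement = (b × p_backlog + n × p_new) / (b + n).

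With B = 178, p_backlog = 20%, p_new = 50%, week 4 gives (71.2 × 0.20 + 27.5 × 0.50) / 98.7 = 27.99 / 98.7 = 28.4%. All intervals:

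| Extraction | Months covered | b | n | Total | Per month | Re-engaged |
|---|---|---|---|---|---|---|
| Week 4 | 1 | 71.2 | 27.5 | 98.7 | 98.7 | 28.4% |
| Month 2 | 1 | 35.6 | 27.5 | 63.1 | 63.1 | 33.1% |
| Month 3 | 1 | 26.7 | 27.5 | 54.2 | 54.2 | 35.2% |
| Month 6 | 3 | 26.7 | 82.5 | 109.2 | 36.4 | 42.7% |
| Month 12 | 6 | 17.8 | 165.0 | 182.8 | 30.5 | 47.1% |
| Month 15 | 3 | 0 | 82.5 | 82.5 | 27.5 | 50.0% |

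Cumulative for implementation: (178 × 0.20 + 330 × 0.50) / 508 = 200.6 / 508 = 39.5%, against 50.0% in the sustainability phase.

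**Step 4: vary the assumptions.**

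- Backlog size (20% and 50%): B = 90 runs from 33.0% to 50.0% (cumulative 43.6%); B = 355 from 24.9% (34.5%); B = 710 from 22.6% (29.5%).
- Smaller difference (35% and 50%, B = 178): 39.2% to 50.0%, cumulative 44.7%.
- No difference (50% and 50%): the proportion is flat, but patients entering per month still fall from 98.7 to 27.5.
- All backlog in the first interval (B = 178, 20% and 50%): (35.6 + 13.75) / 205.5 = 24.0% at week 4, then 50.0%.
- Rates swapped (backlog 50%, new 20%, B = 178): week 4 gives (35.6 + 5.5) / 98.7 = 41.6%, falling to 20.0%.

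The fall in counts needs only a backlog and a steady inflow. The drift in proportions also needs the two groups to differ, and its direction depends on how they differ.

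**Step 5: the same series after the split.** Under every setting with p_new = 50%, newly OOC patients show a flat 50% and 27.5 a month, and the backlog appears as its own group.

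**The case against.** The strongest reply is that this is a descriptive split that an article may leave to a fuller document, and nothing forbids it. That is partly fair. But the article does fix both populations and the reporting split, and it applies the onset argument to analysis ii while leaving it out of the outcomes meant to show change.

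Nurse validation is a second reply. Step 2 uses shared care, travel and other arrangements to confirm OOC status, and reasons for not re-engaging are reported. This may narrow the difference between the groups, and the pace of review may spread the fall in confirmed counts. It does not separate patients by onset.

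Third, the magnitude rests on assumptions. This stands. The inputs do not even align: 178 leavers a year is about 15 a month, against the 25 to 30 used as the flow, and the article does not call those 25 to 30 new cases.

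Several stronger readings are tempting but not supported:

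- A reader might infer that analysis ii removes the whole backlog. It excludes only patients OOC before 2017-2018. Those who became OOC in that year and were still absent at go-live remain, as its comparison group.
- A reader might infer that the backlog is exhausted by the sustainability phase. Core element II ends contact attempts at up to 6 months, but unreached patients stay on the list and nurses may alter the period.
- A reader might infer that the phase comparison is invalid. The formal comparison is analysis iii, which is limited to a window; analysis i describes each phase.
- A reader might infer that the plan will credit any shift to adaptation. It does not say so. It interprets the figures with focus groups and the facilitator's logbook.

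**Conclusion.** The point holds for Aim 1 interim effectiveness and for descriptive analysis i, and for nothing else. As written, both pool a one-off backlog with newly OOC patients, and the split by risk category does not separate them. Counts identified will fall after go-live regardless of performance, given a backlog and a steady inflow. Proportions, contact attempts and time to re-engagement will drift only if the groups differ, by an amount and in a direction that the documents do not give; the percentages above are illustrations, not estimates.

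The consequence is moderate. These outputs are descriptive, the viability rule under Mixed-methods analyses rests on implementation outcome scores, and the statistical comparisons are in analyses ii and iii. It should be corrected because the interim series is there to be read as change over time. The missing five-year limit in analysis i is a smaller mismatch of the same kind: as written, it could admit longer absences than Aim 1 while reporting the same measures.

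**What to change.** 1. Flag each OOC episode as having already met the step 1 criteria at go-live, or as first meeting them afterwards.
2. Report every Aim 1 interim outcome and every analysis i outcome for the two groups separately, and overall.
3. Base statements about change over time on the second group.
4. Apply the five-year visit limit of Aim 1 to analysis i.

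No patient is dropped and no clinical procedure changes. The flag needs only each patient's step 1 status on the day the tool starts. Exact onset dates, if wanted, would need a database look-back longer than the one-year retrospective run planned for analysis ii. The other cost is smaller cells at early time points: about 25 to 30 newly OOC patients in each of the first three intervals if the article's monthly estimate is the flow of new cases, and fewer within each risk category.

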#### Outcomes and related measures

##### Effectiveness

Information to evaluate changes in interim effectiveness outcomes over time will be collected automatically using RISQ and will be extracted for analysis at specific time points during the study (see Table 2). Interim effectiveness refers to effectiveness between the time points in Table 2, as opposed to cumulative effectiveness, which refers to overall effectiveness for the implementation or sustainability phases. These interim effectiveness outcomes include the number of patients identified and confirmed as OOC by nurses. Among OOC patients, we will report the number of patients contacted, successfully re-engaged, and not re-engaged, as well as reasons for lack of care re-engagement. For each OOC-RPT risk category, and overall, we will also provide the number of contact attempts needed to re-engage patients, time to re-engagement, and other clinical and sociodemographic information routinely collected in RISQ.

**Table 2 Tab2:** Data collection schedule

	Pre-implementation	Week 1	Week 2	Week 3	Week 4	Month 2	Month 3	Month 6	Month 12	Month 15
Effectiveness					d	d	d	d	d	d
Feasibility	a, c				a, c	a, c	a, c	a, c	a, c	c
Acceptability	a, c				a, c	a, c	a, c	a, c	a, c	c
Adoption	a, c				a, c	a, c	a, c	a, c	a, c	c
Fidelity	b, c	b	b	b	b, c	b, c	b, c	b, c	b, c	c

a) 36-item questionnaire; b) fidelity checklist; c) focus group; and d) RISQ

##### Implementation

Four implementation outcomes will be studied (Additional file 3): (i) feasibility, i(i) acceptability, (iii) adoption, and (iv) fidelity.

Nurses will complete a 38-item self-administered questionnaire (Additional file 4) to assess implementation outcomes i to iii at various time points (see Table 2), each of which is captured by a 5-item scale. Scales for *feasibility and acceptability* were inspired by Weiner et al.’s pragmatic measures and the TAPP-C (The Arson Prevention Program for Children) compatibility and complexity subscales [29, 30]. These outcomes will be measured separately for each of the core intervention elements (i. identifying and documenting OOC patients, and ii. contacting OOC patients). *Adoption* will be measured using scales from the TAPP-C Adopter Characteristics Questionnaire and the TAPP-C Innovation Characteristics Questionnaire [29]. These questionnaires are comprised of subscales for factors that affect adoption: concern, self-efficacy, attitude, relative advantage, complexity, and compatibility. Given conceptual similarities to feasibility and acceptability, the complexity and compatibility subscales of the TAPP-C were not retained in the study questionnaire. Adoption subscales will focus on evaluating the combined intervention (core elements 1 and ii) so as to limit respondent burden. Justifications for the measures selected are provided in Additional file 3.

*Fidelity* will be assessed primarily through information automatically collected during the routine use of RISQ by nurses, and supplemented with simple checklists (Additional file 4). These self-administered checklists will assess fidelity to each core intervention element and peripheral components that cannot be measured through RISQ (for example, use of and adherence to motivational communication techniques). Nurses will also report on fidelity to motivational communication principles using questions inspired by the Behaviour Change Counselling Scale (BCCS) [18]. RISQ will provide all remaining fidelity information, such as how nurses use the OOC list.

Perceived *barriers and facilitators* to overall implementation, including the implementation outcomes of interest, will be assessed through seven focus groups with nurses. A timeline for these is presented in Table 2. These one-hour discussions will provide specific, actionable information for modifying peripheral components and contextualizing quantitative questionnaire data collected during the study. The focus groups from pre-implementation to month 12 will focus on factors related to implementation, while the focus group at month 15 will concentrate on sustainability of the Lost & Found intervention. Focus groups will be guided by a semi-structured interview schedule (Additional file 4), audio-recorded, and transcribed verbatim for a content analysis.

All modifications to peripheral components of the intervention will be documented in the internal facilitator’s logbook [31]. This will include an explanation of the change made, the actions taken to affect the change (i.e. the planning, engaging, and executing steps of the PEEER cycle), and the outcome of the change (i.e. the evaluating and reflecting steps of PEEER).

Nursing questionnaires will be administered and focus groups will be conducted more frequently during the first half of the project, where changes to peripheral components may be critical to overall implementation and effectiveness outcomes. The timing of data collection is summarised in Table 2 and is consistent with Proctor’s proposed salience of implementation outcomes relative to the implementation stage [23].

#### Data analysis

##### Quantitative analyses

To assess changes in interim effectiveness and nurse-related implementation outcomes throughout the study (Table 2), descriptive statistics (e.g. counts, proportions, medians, and inter-quartile ranges) will be reported.

All subscales for implementation outcomes will be scored using the mean of responses on individual 5-item Likert items. Subscale mean scores will be presented and a Cronbach's alpha will be calculated to report on the internal consistency of each subscale.

Throughout implementation, we will assess fidelity by reporting on the use of the OOC list and RISQ “follow-up” tab, as intended, as well as on adherence to each of the motivational communication principles. Other fidelity measures, such as the relative proportion of Lost & Found activities completed by each nurse (e.g. proportions of phone calls completed), will be drawn from the RISQ database. All analyses will be conducted using R statistical software.

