**Discussion:**

This study will provide preliminary evidence for (1) the utility of our chosen implementation strategies and (2) the effectiveness of the intervention. Ultimately, this information may be used to inform future re-engagement efforts using implementation science in other HIV care centres. In addition, the procedures and measurement tools developed for this study will be foundational to the development of a multi-site, randomised stepped wedge study that would provide more robust evidence in support of the Lost & Found intervention.

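### Cronbach's alpha is planned for each subscale with only four nurses responding, too few for it to say anything useful about internal consistency

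*Protocol article*

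**What the plan says.** Under Aim 1, Participants, the respondents are fixed as every nurse giving HIV care at the clinic: "Participants will include all nurses providing clinical HIV care to patients over the study period (*n* = 4").

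Under Aim 1, Quantitative analyses, the scoring rule is "All subscales for implementation outcomes will be scored using the mean of responses on individual 5-item Likert items". The next sentence says that subscale means will be presented and that Cronbach's "alpha will be calculated to report on the internal consistency of each subscale". It gives no interval and no minimum number of respondents, and does not say whether alpha is computed per round or over all rounds together.

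Table 2 schedules the questionnaire six times: before implementation, at week 4, and at months 2, 3, 6 and 12.

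The abstract's Discussion says that "the procedures and measurement tools developed for this study will be foundational to the development of a multi-site, randomised stepped wedge study".

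**The concern.** The stated purpose of alpha is to describe how well the items of each subscale hang together. That is a statement about the instrument, and alpha estimates it from variation between respondents. Four respondents give 3 between-person degrees of freedom, so the estimate can land almost anywhere, including below zero.

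The feasibility and acceptability scales were modelled on earlier measures rather than taken over unchanged, so their reliability here is a fair question. Alpha is the only reliability coefficient that the article plans. A value that looks high or low by chance would say nothing dependable about tools that the abstract links to the development of a later study. Surveying every nurse at this clinic does not remove the problem, because use at other sites requires inference beyond these four people.

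**Working it through.** **Inputs from the article**
- Respondents: n = 4 (Aim 1, Participants).
- Questionnaire rounds: 6 (Table 2).
- Subscales: feasibility and acceptability are each rated for two core elements ("These outcomes will be measured separately for each of the core intervention elements"), giving 2 × 2 = 4. Adoption lists six subscales and does not retain two, giving 6 - 2 = 4. The total is about 8.
- Items: the Implementation section gives 38 ("Nurses will complete a 38-item self-administered questionnaire") and the Table 2 footnote gives 36 ("a) 36-item questionnaire; b) fidelity checklist; c) focus group; and d) RISQ"). The average is 38/8 = 4.75 or 36/8 = 4.5 items per subscale.

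**Assumptions**
- k = 5 items per subscale, with 3 to 8 as the range.
- The article gives no expected alpha and no target. I take observed values of 0.70 to 0.90, true values of 0.80 and 0.50, and 0.70 as a benchmark.

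The article states no precision for alpha, so there is no figure of its own to reproduce.

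**Step 1: one round.** The Feldt result is (1 - α)/(1 - α̂) ~ F(n - 1, (n - 1)(k - 1)). With n = 4 and k = 5 the degrees of freedom are 3 and 12. The 97.5% and 2.5% points of F are 4.474 and 0.0698. The interval runs from 1 - (1 - α̂) × 4.474 to 1 - (1 - α̂) × 0.0698.

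| Observed alpha | Lower limit | Upper limit |
|---|---|---|
| 0.70 | 1 - 0.30 × 4.474 = -0.34 | 1 - 0.30 × 0.0698 = 0.98 |
| 0.80 | 1 - 0.20 × 4.474 = 0.11 | 1 - 0.20 × 0.0698 = 0.99 |
| 0.90 | 1 - 0.10 × 4.474 = 0.55 | 1 - 0.10 × 0.0698 = 0.99 |

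**Step 2: number of items.** At observed 0.80, k = 3 (3 and 6 df, F = 6.599) gives a lower limit of 1 - 0.20 × 6.599 = -0.32. With k = 8 (3 and 21 df, F = 3.819) it is 1 - 0.20 × 3.819 = 0.24. More items per subscale do not cure the problem.

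**Step 3: how often alpha misleads (k = 5).**
- True alpha 0.80: P(α̂ < 0.70) = P(F < 0.20/0.30) = 0.41, and P(α̂ < 0) = P(F < 0.20) = 0.11.
- True alpha 0.50: P(α̂ ≥ 0.70) = P(F ≥ 0.50/0.30) = 0.23.

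A simulation of 5-point responses (40,000 runs, underlying alpha 0.80, item means 3 to 4.5) was slightly worse, with 45% to 53% of estimates below 0.70. Alpha was undefined, because total scores did not vary, in at most 0.2% of runs.

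**Step 4: pooling all rounds.** This gives 4 × 6 = 24 records from the same four people. Simulation (20,000 runs, true alpha 0.80, k = 5) gives:

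| Share of variance stable within nurse | Central 95% of estimates |
|---|---|
| 0 (records independent) | 0.58 to 0.89 |
| 50% | 0.47 to 0.92 |
| 80% | 0.10 to 0.94 |

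**Step 5: comparison.** For observed 0.80 and k = 5, 30 respondents would give 0.66 to 0.89, and 100 would give 0.73 to 0.86.

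**Step 6: how many coefficients.** If alpha is computed per round, 8 subscales × 6 rounds gives up to about 48 values, and some would be negative by chance.

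**The case against.** The strongest reply is that alpha decides nothing. The viability criterion under Mixed-methods analyses rests on the level and trend of implementation scores, supported by focus-group data. The article sets no threshold for alpha and drops no scale because of it. This stands. A reader might infer that an unreliable alpha undermines the viability decision, but an imprecise alpha changes no score, so the text does not support that.

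A reader might also infer that the scales will pass into the next trial on the strength of alpha. The abstract says only that procedures and tools are foundational to developing that study. It does not say that the scales will be reused unchanged, or that alpha will decide.

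Nor are all the scales shown to be new adaptations. That description fits feasibility and acceptability, while adoption uses scales from existing questionnaires. Additional file 3, which holds the justification for the measures, is not shown.

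Two further replies carry less weight. The Limitations section admits the small sample of nurses, but as a limit on assessing the implementation strategy, not on scale reliability. The article also leaves open whether rounds are pooled, which a fuller plan might settle. Pooling narrows the range, but how far depends on within-nurse stability, which is unknown and cannot be estimated well from four people.

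**Conclusion.** The point holds as a minor one. The article commits to an unqualified alpha per subscale with four respondents, and at that number alpha cannot separate a poor scale from an excellent one. An observed 0.70 is compatible with anything from below zero to 0.98. That conclusion does not depend on the assumed item count, since the interval at observed 0.80 stays very wide from 3 to 8 items. Pooling does not reliably rescue it.

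To say that alpha cannot be estimated at all would go too far, since it can be computed whenever the nurses' total scores differ. The consequence is limited to what the pilot can claim about the reliability of its tools. The size rests on the Feldt model, the assumed alphas and, for pooling, the assumed share of variance that is stable within nurse.

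**What to change.** Replace the sentence on alpha in the quantitative analysis section of Aim 1 in one of two ways. Either drop alpha and state that internal consistency cannot be assessed with four respondents, or report it only with its 95% interval and that same statement. In both cases, defer reliability assessment to the multisite study, where more respondents can be expected.

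This is a one-sentence change that needs no new data. The downside is that the pilot will report no usable reliability coefficient for its subscales.

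Showing each nurse's subscale scores over time beside the mean is an optional addition. With four colleagues at one named clinic, it should be done only if identifiability has been dealt with first.
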